## Abstract

The research aims to evaluate the effectiveness of a computerized cognitive training program in improving executive functions and attention in elementary school children, compared to a traditional paper-and-pencil intervention. The study has been formulated as a randomized controlled trial with pre- and post-intervention measures. For the study, third-grade children with typical development aged between 7 and 9 years will be recruited. Participants will be randomly assigned to the two study arms (control and experimental). The experimental group will participate in a computerized intervention using the NeuronUp cognitive stimulation platform for 8 weeks, twice a week. Sessions will be conducted using computers in the computer lab of the participating educational institution. The active control group will engage in paper-and-pencil cognitive training for the same duration and intensity as the experimental group. Evaluators will be blinded to the assignment, and participants will be blinded to the target intervention. Hypothesis testing will be conducted through ANOVA-MR, and logistic regressions will be implemented to assess the effect of socioeconomic variables on children's performance. These results are expected to contribute to the discussion on the opportunities and benefits offered by cognitive training programs on the cognitive development of typically developing children.

Specifications table

**Table utbl0001:** 

Subject Area:	• Cognitive sciences
More specific subject area:	• Children's Cognitive Development
Name of your method:	Randomized controlled trial to evaluate the effect of a cognitive training program
Protocol name:	Effects of computer-based cognitive training vs. paper-and-pencil-based training on the cognitive development of typically developing children: Protocol for a randomized controlled trial.
Reagents/tools:	• Computer-based cognitive training • Paper-and-pencil cognitive training
Experimental design:	A randomized controlled trial with intra-subject and inter-subject evaluations will feature two parallel groups: an experimental group and an active control group. Pre-test and post-test measures will be conducted. Participants will consist of two third-grade classes, aged 7 to 10 years (*N* = 58). Random allocation will be employed. Primary measures will include neuropsychological tests to assess executive functions (cognitive flexibility, working memory, inhibitory control, planning, and attention). The experimental group will undergo computer-based cognitive training, while the control group will undergo paper-and-pencil cognitive training. The intervention will take place at the educational institution, twice a week in 40-minute sessions, spanning 8 weeks with a total of 16 sessions. Evaluators responsible for pre-test and post-test measurements will be blinded to the allocation. Researchers in charge of the intervention will be blinded to the evaluation results.
Trial registration:	The study was registered in the Office of Research and Scientific Development at University of Tolima under code 50,119.
Ethics:	The randomized controlled trial complies with the ethical parameters defined by the Helsinki Declaration [1], as well as the norms for health research established by the Colombian Ministry of Health [2] in Resolution 8430. Parents and guardians of the children who agree to participate will sign informed consent forms. This randomized controlled trial has been approved by the bioethics committee of University of Tolima, as documented in minutes No. 10 of December 13, 2022.
*Value of the Protocol:	• This protocol is important for verifying the effects of computer-based cognitive training on the development of executive functions in typically developing school-aged children. • This protocol presents a systematic proposal for computer-based training that could contribute to the design of new programs in similar populations. • This protocol presents the necessary methodological elements to facilitate its pre-application in future studies.

## Background

Computer-based cognitive training programs have gained popularity in recent years, offering several advantages over traditional pencil-and-paper interventions. However, there is a strong debate about the effectiveness of computer-based cognitive training programs and the long-term permanence of their effects [3]. This debate has led to positions both for and against the benefits of these programs. Studies suggest that computer-based cognitive training programs produce near transfer effects on cognitive functions, with less evidence for far transfer [4]. Overall, numerous studies have shown encouraging results regarding the improvement of specific cognitive skills and their applicability in daily life and academic settings [5]. However, the effects of introducing these types of programs in school settings with typically developing children are still relatively understudied.

A general review of the literature shows that computer-based cognitive training programs have demonstrated their effectiveness in improving cognitive functioning across multiple dimensions, with compelling results in various populations. For instance, cognitive training programs have shown good results in different populations such as children with learning difficulties or neurodevelopmental disorders [6], and improvements in working memory, attention, and academic performance in children with ADHD [[7], [8], [9], [10]]. Additionally, these programs have led to improvements in executive functions (EF) in children with behavioral, emotional, and social difficulties [11], non-verbal memory in children with intellectual disabilities [12], and reading skills in children with special educational needs [13]. Furthermore, training of working memory has been associated with achievements in mathematics and reading [[5], [14],^15^]. Cognitive training has also been beneficial for adolescents with anxiety and low attentional control, for improving executive functions in preschool children [16], and for children with working memory difficulties [6,17]. Finally, training of executive functions has been effective in neurotypical children [18].

Cognitive training has been widely studied in recent years, and it has been concluded that the success of interventions largely depends on the study design, the training program, the target group, and the selected outcome measures [19]. Important aspects to consider in this type of study include the number of participants, the type of instruments selected to assess the impact of training, the inclusion of an active control group, random assignment of groups [6], and control of study bias risks [20]. In other words, the rigor with which the study is formulated and conducted is crucial.

Given this background, there is a clear need for study protocols with methodological rigor to ensure that the evidence collected on the effects of computerized and paper-and-pencil cognitive training is valid and reliable. Additionally, a rigorous methodological design allows for the study to be replicable in other contexts. The current study protocol was designed in response to this issue.

## Description of protocol

There is strong evidence showing that developmental contexts and human experiences during childhood are determinants of cognitive development [21,22]. Similarly, it has been demonstrated that the family and school environment in the early years of life have a key impact on the development of various cognitive domains, as well as on the function and structure of the brain networks that support them [[23], [24], [25]]. Additionally, it has been observed that children in more vulnerable conditions tend to have poorer performance in their cognitive processes, which influences their academic outcomes [[23], [26], [27]].

These findings have highlighted the need to provide developmental and learning opportunities for children throughout their growth, promoting their cognitive skills [[19], [22]]. This has been a significant challenge in both the fields of cognitive sciences and human development and education. In response to this issue, various intervention programs have emerged in recent years aimed at children with neurodevelopmental disorders as well as typically developing children, such as cognitive training programs. As a result of the emergence of these programs, there has also been a growing number of studies aimed at examining the impact of training programs on children's cognitive abilities to identify the benefits, limitations, and opportunities for improvement of existing programs [[5], [28],^29^]. The present protocol showcases research that seeks to contribute to this developing field of study.

## Cognitive training and brain plasticity

Cognitive stimulation refers to a set of techniques and strategies aimed at improving overall cognitive performance or specific processes and components (such as attention, memory, language, executive functions, and calculation), whether in healthy individuals or in patients with alterations in their central nervous system [19]. In childhood, cognitive stimulation aims to provide children with experiences that support cognitive development in domains that are still evolving, thus promoting learning that the child has not yet acquired [30].

Cognitive stimulation is guided by the principles of transfer and generalization [31] and is supported by mechanisms of brain plasticity—the brain's ability to change in response to experience or environmental stimulation [21]. Brain plasticity facilitates processes such as reorganization of functional interactions among different neuronal groups, the incorporation of new areas into previously established networks, and neuronal adaptability in areas adjacent to affected brain regions [32,33]. While many cognitive stimulation programs targeted at children have been developed in clinical settings, interventions in school and home environments are gaining increasing recognition.

## Computerized programs and paper-and-pencil programs

Cognitive training consists of a series of activities and exercises selected to harness the brain's plasticity, providing individuals with challenging situations that promote new learning and strengthen problem-solving skills. There are essentially two types of cognitive training programs: process-based training and strategy-based training [29]. Process-based training involves repeatedly performing cognitive tasks, typically with increasing difficulty as the individual progresses. This progressive complexity ensures a constant stimulus that promotes cognitive development [17].

Many of these tasks are often based on classical training paradigms such as n-back, go/no go, and the Flanker task, among others [34]. The goal of this type of training is to improve specific functions so that they can be transferred and applied to real-life problems.

On the other hand, strategy-based training teaches procedures and strategies to improve cognitive functions [29], including metacognitive strategies, reading techniques, and self-instructional training, among others.

The advancement of digital technologies has led to the emergence of assistive technologies for cognitive stimulation and rehabilitation, introducing new approaches that have propelled the popularity of computerized cognitive training over traditional paper-based methods. Programs supported by digital interventions, often referred to as 'cognition-supporting technologies,' have shown significant impacts on training various processes such as verbal communication, executive functions, and social participation [[35], [36]]. These programs have evolved from first-generation games and activities to fourth-generation technology today [8,37].

Computerized cognitive training offers several advantages over paper-and-pencil methods, primarily due to the customization and adaptability provided by software. These programs are often more interactive and visually appealing, providing instant feedback on performance and enhancing accessibility across different environments, thereby integrating seamlessly into the subject's routine. They also enable monitoring and tracking of progress, offer a wide variety of tasks, and incorporate more sensory modalities compared to paper-and-pencil activities [34].

Although computerized cognitive training offers these advantages, it does not necessarily completely replace paper-and-pencil training, which can be particularly useful when technology is unavailable, for promoting fine motor skills, or simply to provide variety in training modalities. The choice between one method or another (or a combination of both) may depend on individual preferences, specific training objectives, and the learning context.

The choice of cognitive training as part of a clinical or educational intervention program must be supported by solid evidence. To contribute to the evidence on the uses, scope, and limitations of cognitive training programs, including the comparison between computerized and paper-and-pencil modalities, we have designed a randomized controlled trial protocol. This protocol aims to compare the effects of computerized cognitive training with pen-and-paper activity-based training on various executive cognitive processes (such as working memory, cognitive flexibility, inhibitory control, and planning) as well as basic cognitive processes like attention.

The protocol was developed following the standards and rigor set by the Consolidated Standards of Reporting Trials (CONSORT), which aim to ensure accurate and transparent description of the design, execution, and data analysis of all randomized controlled trials. It also adheres to ethical standards established for studies involving human subjects. The protocol includes the methodological design of the study and provides detailed descriptions of the interventions studied, facilitating replication in future research. Additionally, it incorporates measures to control biases, ensuring the quality and robustness of the collected evidence.

## Specific objectives and hypotheses

The current randomized controlled trial (RCT) aims to evaluate the effect of computerized cognitive training on the executive functions of third-grade neurotypical children, aged 7 to 10 years, compared to paper-and-pencil cognitive training. In response to these research objectives, the following working hypotheses have been formulated:-Null Hypothesis (H_0_): There are no significant differences in executive functions between children receiving computerized cognitive training and those receiving paper-and-pencil cognitive training.-Alternative Hypothesis 1 (H_1_): It is expected that the group of children receiving computerized cognitive training will show greater improvements in their executive functions compared to those receiving paper-and-pencil cognitive training.-Alternative Hypothesis 2 (H_2_): It is expected that the group of children receiving paper-and-pencil cognitive training will show greater improvements in their executive functions compared to those receiving computerized cognitive training.

## Protocol design

The study is designed as a randomized controlled trial with intra-subject and inter-subject evaluations, employing a crossover design involving two simultaneous groups: an experimental group undergoing computerized cognitive training and an active control group undergoing traditional paper-and-pencil cognitive training. Two measures will be administered—one before the intervention (pre-test) and another after the intervention (post-test). Subsequently, following the post-test, the groups will switch interventions. The clinical trial protocol adheres to the CONSORT guidelines [38]. Fig. 1 illustrates the experimental design scheme.

**Fig. 1 fig0001:**
[figure not shown]
Experimental design scheme.

## Criteria for inclusion and exclusion

The target population for the study consists of third-grade children from public elementary schools in Colombia. The following inclusion criteria have been established: 1) Children of both sexes; 2) Currently enrolled in the third grade of elementary school; 3) Aged between 7 years 0 months and 9 years 11 months at the beginning of the study.

The exclusion criteria are defined as follows: 1) Children with uncorrected sensory disabilities that limit their participation in intervention activities; 2) Children diagnosed with psychiatric disorders or neurodevelopmental disorders.

## Sample size calculation

A projected estimate was conducted using G-Power to establish parameters for sample size calculation (see Table 1), based on previous studies that reported moderate to large effect sizes in similar research [39]. This estimation suggests a group size of 29 children, resulting in a total sample size of 58 children.

**Table 1 tbl0001:** Parameters for group size calculation.

Parameter	Value
Effect size	0,75
α confidence level	0,05
Sample power	0,8
Number of groups	2
Number of measures	2
Total sample size	*N* = 58
Sample size per group	*N* = 29

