## Bias control

For bias control, we rely on the bias control tool for controlled trials from the Cochrane organization [56], which defines six domains of bias (see Table 2). We established actions to control the occurrence of the most common types of bias in non-clinical studies, such as selection bias, detection bias, performance bias, attrition bias, and reporting bias [20].

**Table 2 tbl0002:** Risk of Bias Control.

Domain	Mechanism to reduce bias risk
Selection bias	Subjects will be randomly assigned through an online randomization software, with this procedure being overseen by an external researcher.
Performance bias	The researchers responsible for the intervention will be blinded to the assignment and test results. Both the control and experimental groups will participate in an intervention; therefore, the participants will be blinded to the target intervention.
Detection bias	The researcher responsible for administering the pre-test and post-test measures will be blinded to the assignment.
Attrition bias	An intention-to-treat analysis approach will be used. Therefore, instead of excluding participants who did not complete the intervention, all participants will be included in the analysis. Synthetic data imputations will be conducted to project missing data, and subsequently, these results will be compared with the per-protocol analysis, which excludes missing data.
Reporting bias	The results will be published according to the objectives outlined in the protocol, regardless of whether the results confirm the proposed hypothesis or not.

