## Statistical analysis plan

A hypothesis test will be conducted using Mixed-Model Analysis of Variance of Repeated Measures (RM-ANOVA), followed by Bonferroni corrections to examine differences between groups. In this analysis, pre-test and post-test evaluations will act as the within-subject factor (repeated measures), while the comparison between the experimental and control groups will serve as the between-subject factor. Partial eta squared will be used to quantify effect size, assuming variables meet the assumptions of homoscedasticity and normality for parametric tests; otherwise, non-parametric tests will be employed.

To analyze the relationship between participants' performance and various sociodemographic variables acting as potential confounders, multivariate linear regression analysis will be conducted for numerical variables, and logistic regression analysis will be applied for categorical variables.

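### Table 1's 80% power applies to one test at alpha 0.05 with all 58 children analysed, and is not shown to hold after the Bonferroni correction and missing data that the protocol plans for

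*Protocol article*

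**What the plan says.** The Protocol article, Sample size calculation, reports a G-Power estimate "based on previous studies that reported moderate to large effect sizes in similar research". Table 1 lists "Effect size 0,75", "α confidence level 0,05" and "Sample power 0,8", with two groups and two measures. The conclusion is "This estimation suggests a group size of 29 children, resulting in a total sample size of 58 children". The table does not say whether 0.75 is Cohen's d or Cohen's f, which test was entered, whether it was two-sided, or what pre-post correlation was used.

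Three other places bear on this figure:

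- **Statistical analysis plan.** The planned test is a mixed repeated-measures ANOVA in which "pre-test and post-test evaluations will act as the within-subject factor (repeated measures") and the arm is the between-subject factor. Bonferroni corrections follow. The set of comparisons they cover is not defined.
- **Specifications table, Experimental design.** "Participants will consist of two third-grade classes, aged 7 to 10 years", with N = 58. The primary measures cover five domains: cognitive flexibility, working memory, inhibitory control, planning and attention. Outcome measures describes eight tests for them. No single primary outcome is named.
- **Bias control, Table 2, attrition row.** Analysis is by intention to treat, and "Synthetic data imputations will be conducted to project missing data".

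**The concern.** A power statement is useful only if it belongs to the test that will be run, at the alpha that will be applied, on the number of children who will supply data. Three things here raise doubt.

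- The printed inputs do not identify one calculation. A reader who enters 0.75 as f with two groups and two measures in a repeated-measures module gets a far smaller number than 58.
- Table 1 uses one alpha of 0.05, while the plan has five primary domains and a Bonferroni step.
- Planned enrolment equals the calculated number, so there is no margin for the missing data that Table 2 foresees.

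The stake is how results are read. The hypotheses set no difference against superiority in either direction. A reader would weigh a non-significant result against the stated 80%, and that figure may not describe the analysis reported.

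**Working it through.** **Inputs from the documents.** Effect size 0.75, alpha 0.05, power 0.8, two groups, two measures, 29 per arm (Table 1); five primary domains (Specifications table); eight tests (Outcome measures). **Assumptions.** Two-sided testing, because the two alternative hypotheses point in opposite directions; pre-post correlation rho of 0.3, 0.5 or 0.7; loss of 10%, taken as 26 per arm; Bonferroni divisor of 5 or 8.

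**1. Reproducing 58 as a t-test.** The noncentrality is δ = d·√(n/2), with 2n − 2 degrees of freedom.

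- n = 28: δ = 0.75 × √14 = 2.806, critical t 2.005, power 0.787.
- n = 29: δ = 0.75 × √14.5 = 2.856, critical t 2.003, power 0.801.

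So 29 per arm is the smallest number that reaches 80%. A one-sided test needs 23 per arm and does not match.

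**2. Reproducing 58 as the group-by-time interaction.** With m = 2 measures, λ = N·f²·m/(1 − rho). If 0.75 is the difference in change in single-time-point SDs, then f = 0.75/4 = 0.1875. At rho = 0.5, λ = 58 × 0.1875² × 2/0.5 = 8.156 = 2.856². This is the same test with the same power: 0.801 at N = 58 and 0.787 at N = 56.

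**3. Other repeated-measures readings (two groups, two measures, rho 0 to 0.8).**

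| Reading of 0.75 | Interaction, N | Between-groups, N |
|---|---|---|
| f = 0.75 | 6–10 | 10–16 |
| d = 0.75, f = 0.375 | 10–30 | 30–54 |

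None of these gives 58.

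**4. Power of the planned group-by-time test.** With two time points this is a t-test on change, with standardised effect 0.75/√(2(1 − rho)): 0.634, 0.750 and 0.968 for rho 0.3, 0.5 and 0.7. Power is per test. The loss rows are complete-case figures.

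| Setting | rho 0.3 | rho 0.5 | rho 0.7 |
|---|---|---|---|
| 29 per arm, alpha 0.05 | 66% | 80% | 95% |
| 29 per arm, alpha 0.05/5 = 0.01 | 41% | 58% | 84% |
| 29 per arm, alpha 0.05/8 = 0.00625 | 34% | 51% | 80% |
| 26 per arm, alpha 0.05 | 61% | 76% | 93% |
| 26 per arm, alpha 0.01 | 36% | 52% | 79% |

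**5. ANCOVA on the same data.** Under randomisation the expected post-test difference equals the expected difference in change. Adjusting the post-test for the pre-test gives a standardised effect of about 0.75/√(1 − rho²): 0.786, 0.866 and 1.050. Because 1 − rho² = (1 − rho)(1 + rho) never exceeds 2(1 − rho), this is at least as powerful as the change test at every rho.

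| ANCOVA setting | rho 0.3 | rho 0.5 | rho 0.7 |
|---|---|---|---|
| 29 per arm, alpha 0.05 | 84% | 90% | 98% |
| 26 per arm, alpha 0.05 | 79% | 86% | 96% |
| 29 per arm, alpha 0.01 | 63% | 73% | 90% |

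**The case against.** The strongest reply is that nothing is miscalculated. 29 per arm gives 0.801, and step 2 shows that the planned interaction test gives exactly the same N under a plausible correlation. A reader might infer that the second measure never entered the calculation, or that 80% power fails for the repeated-measures ANOVA as such. The documents support neither inference. How 58 was obtained cannot be told from Table 1. The repeated-measures test has less power than stated only if rho is below 0.5, and more if rho is above it. No correlation is given.

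The divisors and the loss rate are also assumptions. The Bonferroni sentence may mean follow-up contrasts within one ANOVA rather than correction across outcomes, and no loss rate is stated. With rho at 0.8, even a divisor of 8 leaves 95% power at 29 per arm. Nor does the protocol say that a null result will be read as equality; it promises publication whatever the outcome.

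These points stand, and they limit the conclusion. They do not remove it. In either matching reading, the calculation is for one test at 0.05 with every child contributing, while the same article names five primary domains, a Bonferroni step and missing data. Imputation keeps children in the analysis but does not in general restore the information lost with their missing scores.

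**Conclusion.** The figure of 58 is reproducible, but its basis is not stated, and the 80% is not shown to hold for the analysis as planned. It is supported for a single two-sided test at alpha 0.05 with 29 children analysed per arm, and for the group-by-time test only if 0.75 is a difference in change in single-time-point SDs and rho is at least 0.5.

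The size of any shortfall depends on quantities that the documents do not give. If Bonferroni runs over the five domains, group-by-time power is between 41% and 84% for rho from 0.3 to 0.7. A 10% loss alone puts it between 61% and 93%. At the favourable end there is no shortfall, so it would be wrong to say that the trial is underpowered. This is a gap in the justification that should be closed before data are seen. It is not an arithmetic error, and it does not invalidate the sample size.

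**What to change.** Keep N = 58 and make these changes:

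1. **Restate Table 1.** Give the effect metric, the test, the sidedness and rho, or delete the row for the number of measures if the calculation was a two-sample t-test.
2. **Qualify the 80%.** Say that it applies to one test at alpha 0.05 with no loss. Beside it, report power or the detectable effect after the planned multiplicity correction and the expected loss, over a range of rho.
3. **Define the multiplicity.** Either state the family that Bonferroni covers or, as an option, name one primary endpoint. The second is a design choice for the investigators, since it changes the status of the other domains.
4. **Change the model.** Analyse the post-test by ANCOVA adjusted for the pre-test score instead of the group-by-time interaction. For one test this gives 84%, 90% and 98% at 29 per arm, and 79%, 86% and 96% at 26 per arm. It does not by itself pay for a five-fold Bonferroni correction at low or middling rho (63% and 73% at rho 0.3 and 0.5), so point 3 is still needed.
5. **Add one sentence on interpretation.** A non-significant difference does not show that the two training modes are equivalent.

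No extra children or assessments are needed, because the pre-test is already collected. The cost is a less favourable stated power and an amended analysis section, not only a reworded table.
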